### Dissemination

The study protocol was registered at ClinicalTrials.gov (identified as NCT04745286). The results will be available and disseminated to all participants, investigators, and healthcare providers in the form of summary documents, presentations on the Internet. The data set analyzed in the current study will be obtained from the corresponding author upon reasonable request.

### Sample size calculation and statistical analysis

According to previous studies, the incidence of atelectasis is approximately 90% in patients pre-oxygenated with 100% oxygen within a few minutes after anesthesia [1, 4, 33, 39]. We estimate that the incidence of atelectasis is 85%, and the preoperative administration of S-ketamine can reduce the incidence of atelectasis to 60%. The sample size was calculated by PASS 15.0. Finally, 50 cases in each group will be estimated to provide 80% power with a significance level *α* of 0.05, allowing for a dropout rate of 5%.

Statistical analysis will be performed using SPSS 24.0. Values will be expressed as mean ± standard deviation ($$\overline{x }$$±s), median and interquartile range (IQR), and percentages according to different distribution types. After testing for normality of continuous variables, Student’s *t*-test or the Mann–Whitney *U*-test will be used for comparison between and within groups, as appropriate. Categorical variables will be analyzed using the chi-square test or Fisher’s exact test. All statistical analyses in our study will be conducted with a bilateral test, and statistical significance will be set at *P* < 0.05. We will exclude patients whose primary data are missing. Both intention-to-treat analysis and per-protocol analysis will be conducted in this study.

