Among all the detection methods of pulmonary disease, lung ultrasound, as a bedside, non-invasive, diagnostic tool, has been increasingly used in the assessment of atelectasis during surgery. Furthermore, it has advantages such as convenience and rapidity and it is radiation-free [28–31]. It has a reliable sensitivity of 93% and specificity of 100% [32].

Previous studies on atelectasis during anesthesia mostly focused on the influence of respiratory parameters such as tidal volume, respiratory rate, inhaled oxygen concentration, positive end-expiratory pressure (PEEP), and the effects of manipulation or mechanical expansion on postoperative atelectasis [7, 33–35]. To date, there is only a little evidence available for pre-treatment with medicine for atelectasis during general anesthesia. The primary objective of this study is to assess whether a small dose of S-ketamine can reduce the incidence of atelectasis after intubation, and further investigate the effects of preventing the early formation of perioperative atelectasis and PPCs.

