### Pulmonary ultrasonography

A well-trained blinded anesthesiologist will perform all lung ultrasound scans using SonoSite M-Turbo with a 5–12-MHz linear transducer. Patients will be scanned in the supine position following the lung ultrasound method described by Sun et al. [37]. Briefly, six regions will be scanned in each hemithorax. Scans 1 and 2 will be performed in the clavicle midline, scans 3 and 4 will be performed in the axillary midline, and the intercostal scans (scans 5 and 6) will be performed at the fifth and sixth intercostal spaces in the posterior axillary line. A linear probe will be placed parallel to the ribs, and the intercostal space of each region will be scanned sequentially from right to left, cranial to caudal, and anterior to posterior within 2 min.

The video clips of each region will be stored on a portable hard drive for offline analysis. Scoring criteria of B-lines are as follows: B-lines will be categorized into four grades (0–3): B0, normally ventilated areas with lung sliding sign: A-line and isolated B-lines (< 3); B1, mild reduction in lung ventilation/moderate loss of lung tissue gasification: B-lines (≥ 3) with clear boundary, regular distribution, and spacing ≥ 7 mm, or irregular, clear interval; B2, severe reduction in lung ventilation/severe lung gasification: multiple coalescent B-lines spaced ≤ 3 mm and continuous fusion; and B3, atelectasis/pulmonary consolidation: tissue-like signs, fragment signs, and bronchial inflation signs appear.

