### Outcome measurement

#### Primary outcome

Total LUS at T2.

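### The 80% power is calculated for incidence of atelectasis (85% vs 60%), not for the primary outcome, total lung ultrasound score at T2, whose power is unstated

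*Protocol article*

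**What the plan says.** - **Objective** (protocol article, Abstract and Background): to "assess whether a small dose of S-ketamine can reduce the incidence of atelectasis after intubation". This is a yes/no outcome per patient.
- **Sample size** (Sample size calculation and statistical analysis): "We estimate that the incidence of atelectasis is 85%, and the preoperative administration of S-ketamine can reduce the incidence of atelectasis to 60" per cent. The section continues: "Finally, 50 cases in each group will be estimated to provide 80% power with a significance level" of 0.05, with a 5% dropout allowance. Tests are two-sided and allocation is 1:1.
- **Primary outcome** (Outcome measurement): "Total LUS at T2". The Abstract, Table 1 and the Discussion name the same outcome and time point.
- **Score** (Pulmonary ultrasonography): six regions in each hemithorax, each graded 0 to 3. The total over 12 regions therefore runs from 0 to 36. Only the top grade carries the label atelectasis: "B3, atelectasis/pulmonary consolidation: tissue-like signs, fragment signs, and bronchial inflation signs appear". No rule turns the regional grades into a yes/no classification of the patient.
- **Other T2 outcomes** (Secondary outcomes): regional LUS, blood gases, plateau pressure and dynamic compliance. Atelectasis as an event appears only as one component of the postoperative pulmonary complications at 2 h and 24 h after surgery.
- **Analysis**: continuous variables by t-test or Mann-Whitney test, categorical variables by chi-square or Fisher's exact test. No mean difference, SD or effect size for LUS appears anywhere in the article.

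**The concern.** Objective and sample size concern one variable, and the primary outcome is another. The 80% power is a property of a two-proportion comparison that is not listed among the T2 outcomes, while the primary test compares a score.

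Two things are at stake. First, a null result on total LUS could not be read against the 80% figure, because nobody has said what LUS difference the trial was built to detect. Second, a positive result on total LUS would not by itself answer the question as the objective words it. Score and incidence can diverge: twelve regions at grade 1 give a total of 12 with no region graded as atelectasis, and four regions at grade 3 with the rest at 0 also give 12.

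**Working it through.** **Inputs from the article:** rates 0.85 and 0.60; two-sided alpha 0.05; power 80%; 1:1 allocation; dropout 5%; 12 regions graded 0–3. **Not in the article:** the LUS difference and SD. Standardised differences (d, in SD units) are therefore an assumption, shown as a range.

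**Step 1. Reproduce the stated 50 per arm.** Two proportions, unpooled variance:

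n = (1.960 + 0.842)² × (0.85 × 0.15 + 0.60 × 0.40) / 0.25² = 7.849 × 0.3675 / 0.0625 = 46.2, rounded up to 47.

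With dropout: 47 / 0.95 = 49.5, rounded up to 50, the stated figure. The pooled-variance formula gives 49, or 52 with dropout, which is close. The arithmetic for incidence is sound, and the 50 is evidently a two-proportion result.

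**Step 2. Evaluable patients for the primary test.** 50 × 0.95 = 47.5, taken as 47 per arm.

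**Step 3. Difference in total LUS detectable with 80% power.**

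- t-test, normal approximation: d = (1.960 + 0.842) × √(2/47) = 0.578. With the t distribution: 0.584. Both round to 0.58 SD.
- Mann-Whitney with normally distributed scores (relative efficiency 0.955): 0.584 / √0.955 = 0.598, about 0.60 SD.

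**Step 4. t-test power for total LUS at 47 per arm, over assumed differences** (t distribution; the normal approximation is about one point higher at most):

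| Assumed difference (SD) | Power |
|---|---|
| 0.3 | 30% |
| 0.4 | 48% |
| 0.5 | 67% |
| 0.6 | 82% |
| 0.7 | 92% |
| 0.78 | 96% |

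The 0.78 row is one way to link the two variables. If atelectasis meant exceeding a single threshold on a normally distributed score, 85% against 60% would imply a shift of 1.036 − 0.253 = 0.783 SD. The article states no such link, and it supports no other row of the table either.

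**Step 5. Look for incidence at T2 among the listed outcomes.** None of the T2 outcomes is a proportion of patients with atelectasis. The regional grades that could yield one are recorded, but the article neither defines nor lists it.

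**The case against.** The strongest reply is that the trial may be adequately powered. Under the single-threshold reading, the rates used for sizing imply about 0.78 SD and 96% power on LUS, since a score usually carries more information than its dichotomy. This stands as far as it goes: a reader might infer from the mismatch that the trial is underpowered, and the document does not support that. Equally, it gives nothing that establishes 0.78 SD, so the reply does not restore the 80% claim.

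A reader might also infer that the objective goes untested. That is too strong. Regional grades, including the grade labelled atelectasis, are compared at T2 as a secondary outcome, and the Discussion words the aim as alleviating atelectasis 15 minutes after intubation, which total LUS does address. What is missing is narrower: a patient-level incidence at T2.

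A third temptation is to discount 85% and 60% by the 93% sensitivity quoted for lung ultrasound in the Background and recompute the power. The article does not say whether the two rates are true or ultrasound-detected, so the adjustment might count sensitivity twice. It would also concern a test that is not the primary one.

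Finally, the primary outcome and its time point are named consistently in four places, so an incidence put forward later as the main result would visibly not be prespecified.

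It could be said that an analysis plan may settle the matter. But the article does not leave the sample size basis open. It states one, for a variable other than its own primary outcome. A later document could add a justification for LUS, but the article's text would still need correcting.

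**Conclusion.** The concern holds as a misalignment. The stated 80% power belongs to a comparison of incidence, 85% against 60%, which matches the objective but is neither the primary outcome nor any listed T2 outcome. For the primary test the 80% has no stated basis. Power for total LUS is unknown: 80% is reached at about 0.58 SD (t-test) or 0.60 SD (Mann-Whitney), and over 0.3 to 0.78 SD the t-test power runs from about 30% to 96%. These figures assume 47 evaluable per arm and roughly normal scores with equal SD.

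Total LUS is a reasonable measure of the extent of aeration loss, so the choice of outcome is not the fault. A lower mean LUS would not by itself show that the incidence of atelectasis fell. Because the trial relies on this power figure to interpret its main result, it should be corrected.

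**What to change.** 1. Keep total LUS at T2 as primary. Replace the 80% statement with the LUS difference that 50 per arm (47 evaluable) can detect: about 0.58 SD by t-test or 0.60 SD by Mann-Whitney, two-sided alpha 0.05. State the SD and the difference on the score scale as assumptions, with a range and a reason why that difference is plausible and worth detecting. Without that reason, the change only relabels the number.
2. Reword the primary objective as loss of aeration measured by total LUS at T2.
3. Prespecify a patient-level incidence of atelectasis at T2 from the recorded regional grades as a secondary outcome, for example at least one of 12 regions graded B3, with risk difference and 95% CI. Cite the 85% against 60% calculation for it only if those rates are justified for that definition; nothing in the article ties them to it.

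The alternative is to make a defined incidence at T2 the primary outcome. Either way, objective, outcome and power must concern one variable.

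**Cost:** changes of wording and one derived variable. Regional grades and video clips are already collected, so no further patients or scans are needed. The planned recruitment period ends in 2022, so the changes may now belong in the analysis plan and the report. They should be fixed and dated before unblinding, with no assumption drawn from the trial's own group comparison.

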### Interventions

Patients will be intravenously infused with the label-covered trial agent 5 min before induction, and all patients will undergo a standardized general anesthesia and analgesia protocol. Lung ultrasound scans will be performed at three points in each patient: immediately after radial artery puncture (T1), 15 min after tracheal intubation (T2), and before extubation (T3). Three arterial blood samples will be obtained through radial artery puncture at each time point (T1, T2, T3), and blood gas measurements will be performed immediately using a standard technique (ABL800).

Agent preparation method: S-ketamine group (group 1): S-ketamine (50 mg; 2 mL) will be diluted with normal saline to 5 mL in an opaque 5-mL syringe (10 mg mL^−1^). Normal saline group (group 2): 5 mL of normal saline. Both will be labeled as “study agents” and injected with a dose of 0.025 mL kg^−1^.

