#### Other indicators to be recorded

Baseline value

General information of patients: age, height, weight, BMI, smoking history, ASA, type of operation, complications, types, and severity of complications.

Anesthesia-related variables: duration of apnea during artificial airway establishment (recorded by stopwatch), laryngoscope insertion times, liquid volume (from entering the room to T2).

Intraoperative indicators: total LUS at T1; arterial blood gas analysis results (PaCO_2_, PaO_2_) and PaO_2_/FiO_2_ at T1; mechanical ventilation parameters (tidal volume, ventilation frequency, and FiO_2_).

(2)Other indicators

Vital signs (pulse, BP, HR, and SpO_2_) at each time point (T1, T2, and T3).

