## Discussion

In this prospective randomized controlled trial, we intend to verify whether using a small-dose S-ketamine before induction can alleviate atelectasis 15 min after tracheal intubation under general anesthesia and to further study the effect of low-dose S-ketamine on PPCs. To our knowledge, to date, this is the only randomized clinical trial of preoperative agents on atelectasis. This will possibly provide a simple and feasible new method on agent prevention and direct clinical evidence for anesthesiologists to conduct intraoperative lung protection strategies. We will use the new non-invasive lung ultrasound technology as a guide for the diagnosis of atelectasis, which has many advantages, such as not being restricted by time or venue and without radiation. The reasons for choosing lung ultrasound scores (LUS) at 15 min after endotracheal intubation as the primary outcome are as follows: (1) previous studies showed that atelectasis has already occurred at this moment after induction and pre-oxygenation with 100% oxygen [40]; (2) this period is within the active duration of a single small dose of S-ketamine, and the effect of operation time and extubation on atelectasis can be excluded; (3) lung ultrasound can detect atelectasis in real-time, and LUS can accurately reflect the pulmonary state. In addition, to analyze the effects of the intervention on gas exchange (PaCO_2_, PaO_2_, and PaO_2_/FiO_2_) in detail, we performed blood gas measurements at three time points (T1, T2, T3). There are limitations in this trial: (1) we will study only the effects of a small dose of ketamine on anesthesia-induced atelectasis, but will not compare the effects of different concentrations of ketamine; (2) ultrasound assessment depends on the operator and reviewer, which may cause subjective bias. However, in order to reduce this bias, all the researchers involved in the pulmonary assessment will be blinded to the allocated information, and all intercostal spaces will be carefully scanned to avoid missing any abnormal findings. In addition, the ultrasound images for each lung region will be analyzed by two experienced radiologists; (3) this is a single-center trial and may have selection bias.

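### The tests named for within-group comparisons are independent-samples tests: Mann-Whitney U is invalid there, and Student's t is valid only if its paired form is meant, which is not stated

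*Protocol article*

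**What the plan says.** The statistical paragraph of the protocol article (Sample size calculation and statistical analysis) gives one rule for all continuous variables. The choice is made "After testing for normality of continuous variables", and then Student's t-test or the Mann-Whitney U-test "will be used for comparison between and within groups, as appropriate". All analyses are "conducted with a bilateral test, and statistical significance will be set at *P* < 0.05". The article names no paired t-test, Wilcoxon signed-rank test, Friedman test, repeated-measures analysis of variance or mixed model.

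The data to which a within-group comparison would apply are repeated measurements:

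- Interventions: "Lung ultrasound scans will be performed at three points in each patient", with an arterial blood sample at each of the same points.
- Table 1 lists total lung ultrasound score and blood gases at T1, T2 and T3, and plateau pressure and dynamic compliance at T2 and T3.
- Other indicators to be recorded: pulse, blood pressure, heart rate and oxygen saturation at T1, T2 and T3.

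The primary outcome is "Total LUS at T2", a single time point compared between the two arms.

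**The concern.** A comparison between arms involves different patients, and both named tests suit it. A comparison within an arm involves the same patients measured more than once. The statistical paragraph does not name the time points for within-group comparison, but the design offers no within-arm contrast that is free of dependence. T1, T2 and T3 are measured on one patient, and the 12 chest regions also lie within one patient.

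Mann-Whitney U assumes two independent samples, so on the non-normal branch of the rule the plan has no valid within-group test. That branch could well apply to the ultrasound score, which is built from ordinal grades of 0 to 3. On the normal branch, the ordinary two-sample t-test ignores the covariance between a patient's two values and so uses the wrong variance for the change.

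At stake are the p-values for changes over time within an arm, for example from before induction to 15 minutes after intubation. A statistical analysis plan that follows the sentence inherits the problem, and one that departs from it contradicts the published protocol. This is a stated choice of test, not detail left for later.

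**Working it through.** **Inputs.** From the article: 50 patients per group, two-sided 5% level, 80% power, 5% dropout, atelectasis incidence 85% versus 60%. Assumed, because the article gives neither: within-patient correlation ρ of 0.3, 0.5 or 0.7, and a within-group change of 0.4 SD. The data are taken as bivariate normal with equal SD at both time points.

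**The plan's own figure.** The sample size with unpooled variance is (1.96 + 0.842)² × (0.85×0.15 + 0.60×0.40) / 0.25² = 46.2, so 47 per group. Then 47/0.95 = 49.5, so 50. The figure reproduces (pooled variance gives 49, then 52). It contrasts two independent proportions and contains no within-patient quantity, so this point does not touch it.

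**Standard error of a change (SD units).** The independent-samples formula gives √(2/50) = 0.200. The correct value is √(2(1−ρ)/50). The ratio is 1/√(1−ρ):

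- ρ = 0.3: 1/√0.7 = 1.20
- ρ = 0.5: 1/√0.5 = 1.41
- ρ = 0.7: 1/√0.3 = 1.83

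**True type I error at nominal 5%.** Because the test statistic has variance 1−ρ instead of 1, the error is 2 × [1 − Φ(1.96/√(1−ρ))]. Simulation with n = 50 (20,000 runs for the t-tests, 5,000 for Mann-Whitney, 2,000 for signed-rank) agrees:

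| ρ | Formula | Two-sample t | Mann-Whitney U | Paired t | Signed-rank |
|---|---|---|---|---|---|
| 0.3 | 0.0191 | 0.0197 | 0.0196 | 0.048 | 0.052 |
| 0.5 | 0.0056 | 0.0060 | 0.0072 | 0.049 | 0.045 |
| 0.7 | 0.0003 | 0.0004 | 0.0004 | 0.048 | 0.044 |

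At ρ = 0 the two approaches agree, at about 0.05. Only a negative correlation would reverse the direction: at ρ = −0.2 the formula gives 0.074.

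**Power for a 0.4 SD change, by simulation.**

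| ρ | Two-sample t | Mann-Whitney U | Paired t | Signed-rank |
|---|---|---|---|---|
| 0.3 | 0.51 | 0.49 | 0.65 | 0.62 |
| 0.5 | 0.51 | 0.48 | 0.79 | 0.76 |
| 0.7 | 0.51 | 0.48 | 0.95 | 0.95 |

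A separate simulation of 3,000 runs gives 0.63 for the signed-rank test at ρ = 0.3; the difference is simulation error. The independent-samples tests stay near 0.5 whatever ρ is, because their rejection threshold is 1.96 × 0.200 = 0.39 SD, almost exactly the assumed change.

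**A larger change.** For 0.8 SD the two-sample statistic is centred on 0.8/0.200 = 4.0. Its power is at least Φ(4.0 − 1.96) = Φ(2.04), about 0.98, for any ρ from 0 upwards. The loss is therefore material for moderate changes and small for large ones.

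**The case against.** The strongest reply is that little depends on these tests. No declared primary or secondary outcome is a change within an arm. The outcomes are values at T2 or T3, or incidences at 2 h and 24 h, and T1 values are listed only among the other indicators. The question is the effect of S-ketamine, which is a between-arm contrast. All of this stands and limits the consequence, but the article does plan within-group comparisons and names tests for them.

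A second reply is that Student's t-test can include its paired form and that the sentence leaves room for judgement. This stands in part: the t-test wording is ambiguous rather than certainly wrong. It does not help Mann-Whitney U, which has no paired form, and the only selection rule stated concerns normality, not pairing.

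A third reply is that the illustration depends on an assumed 0.4 SD change and normal data. That is fair. The article says atelectasis develops within minutes of induction in most patients, and abnormal preoperative chest imaging is excluded, so the T1 to T2 change in score may be large. The wrong test would then usually still detect it. A score near its floor at T1 may also depart from the normal model used here.

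A reader might infer several stronger things that the document does not support:

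- **False positive findings.** With positive correlation the p-values are too large, not too small.
- **Wrong error bars or summaries.** The article reports mean and SD, median and IQR, and percentages, none of which depends on the test chosen.
- **A treatment claim built on significance in one arm and not in the other.** No such reading is planned, and paired tests would not make it valid.
- **A need for McNemar's test on the 2 h and 24 h incidences.** Within-group comparison is mentioned only in the sentence on continuous variables.

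**Conclusion.** The point holds in limited form. The article assigns tests for independent samples to comparisons on the same patients. This is definite for Mann-Whitney U and conditional for Student's t, which is acceptable only if the paired form is intended. The result is conservative inference and lost power on within-arm changes, of the size shown above. Those figures rest on assumed correlations of 0.3 to 0.7, an assumed 0.4 SD change, normal data and 50 patients per group. The direction rests on the correlation being positive, which is usual for repeated measurements on one patient but is not stated in the article.

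No between-group result is affected, whether primary or secondary. The wording should be corrected, but it does not threaten the trial's main conclusion.

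**What to change.** Replace the sentence with one that separates the two kinds of comparison:

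- Between groups at a given time point: Student's t-test or Mann-Whitney U-test, as now.
- Within a group, between two time points: paired t-test or Wilcoxon signed-rank test, with normality judged on the within-patient differences.
- Within a group, across T1, T2 and T3: alternatively, a repeated-measures or mixed model that accounts for the patient.

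Add that claims about the treatment rest on the between-group comparisons. The change costs one or two sentences. It needs no new data or patients and leaves the sample size as it is.
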